### Analysis of endpoints

In equivalence testing a maximum clinical difference (Δ_T_) is pre-specified at a level within which the two treatments can be considered not to differ in any clinically meaningful way. Therefore, the relevant null hypothesis is that a difference of greater than Δ_T_ exists in either direction, H0: Δ ≤ -Δ_T_ or Δ ≥ Δ_T_, and the trial is targeted at disproving this in favour of the alternative that no clinical difference exists, HA: -Δ_T_ < Δ < Δ_T_**.** FDA regulations recommend both a treatment received (per-protocol) and intention to treat analysis, aiming to demonstrate equivalence [37]. Use of an ITT approach as in a superiority trial sometimes increases the chance of falsely claiming equivalence [38,39]. Initially, a per-protocol analysis will be undertaken where only the patients who received their allocated treatment will be analysed and those patients who did not, will be excluded from the analysis. Following this an intention to treat analysis will be carried out where all randomised patients will be analysed according to the treatment they were randomised to.

The result of the analysis of the primary endpoint should be one of the following:

● The confidence interval for the difference between the two treatments lies entirely within the equivalence range, -Δ_T_ to Δ_T,_ so that equivalence may be concluded with only a small probability of error.

● The confidence interval covers at least some points that lie outside the equivalence range, so that differences of potential clinical importance remain a real possibility and equivalence cannot safely be concluded.

● The confidence interval is wholly outside the equivalence range (though this is likely to be rare).

As well as assessing if equivalence is demonstrated in either case this will also form part of an additional sensitivity analysis to assess the range of potential biases that could have resulted from loss to follow-up, protocol deviations, withdrawal (and mortality). Numerical and graphical summaries of all the data will be compiled, including descriptions of missing data at each level. Estimates of treatment effect will be reported with 95% confidence intervals and a figure showing confidence intervals and margins of equivalence will also be presented. Our main analytical methods will be generalised linear models, and all analyses will adjust for important baseline co-variants to maximise precision.

The Olerud & Molander Ankle Score at 6 months is the primary outcome in this study and will be compared between treatment groups as the dependent variable in a linear regression model for the primary analysis. The treatment difference will be based on the estimates of the adjusted means and 95% confidence intervals. The Olerud & Molander Ankle score will also be presented as an ordinal outcome in a secondary analysis using ordered logistic regression or non-proportional odds models, depending on the validity of the proportional odds assumption, will be carried out. Secondary outcome measures will be similarly analysed with logistic regression models being used for categorical data and linear regression models for continuous data. Time to event data (e.g. time to discharge) will be analysed using a log-rank test. Any patients who have not experienced an event at the time point of interest or withdrew will be censored. The proportion in each treatment group experiencing an event over time will be illustrated using a Kaplan-Meier curve. The p-value and a hazard ratio with its 95% CI from a Cox proportional hazards model will also be presented. The proportional hazards assumption across treatment arms will be checked graphically using a log-cumulative hazard plot. A data analysis plan will be agreed with the Independent Data Monitoring Committee.

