### Intervention

#### Manipulation under anaesthetic in theatre and application of Close Contact Cast (CCC)

Standardisation of the casting materials, cast design and application, and moulding technique will be achieved by surgeon instruction (training session and access to training videos and documentation). The method of closed fracture manipulative reduction of deformity will be at the discretion of individual surgeons and this falls within the common contemporary skills set of senior surgical trainees and consultants. The CCC is applied once major swelling has subsided at a similar time to that when open surgery would be considered. The use of specific moulding points and sited pressure pads prevents fracture displacement whilst minimising the risk of skin damage. In the weeks following the initial cast application, and after any re-applications of the cast (if required), participants in the CCC group will require monitoring X-rays to check maintenance of fracture position.

It is possible that in some cases, after randomisation, the intervention delivered will necessarily be changed. We anticipate the following:

● After randomisation at the point of intervention with anaesthesia commenced, the temporary cast is removed. The ankle skin condition may have deteriorated such that the surgeon considers one or all necessary surgical incisions to be unsafe. If randomised to ORIF, an alternative treatment* would be given.

● After randomisation at the point of intervention with anaesthesia commenced, a fracture may prove irreducible by closed manipulation. The surgeon would necessarily proceed to open surgical reduction. If that is required, internal fixation would be undertaken.

● If there is an unacceptable loss of position by either treatment method prior to fracture healing, the surgeon will adopt the treatment approach* best judged to achieve a favourable outcome.

● Very rarely a combination of bone and skin fragility and gross joint instability will exclude either intervention. The surgeon will apply a temporising external fixator and definitive treatment* will be at the surgeon’s discretion.

* alternative treatments include: i) traditional plaster cast, ii) external fixation iii) ORIF. CCC will be excluded as an option outside the group randomised to CCC.

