### Sample size

Given the paucity of data in the published literature the feasibility pilot data have been used as a primary source to inform estimates of variance and treatment effects measured using the Olerud & Molander score, and a range of secondary outcomes. We have tested the sensitivity of these estimates against data available in the published literature.

Although the original sample size estimate was based on a difference in proportions this was modified by the DMEC as data from the pilot study confirmed data to be normally distributed and that analysis based on a continuous score would be more efficient and meaningful. Parameters for the sample size were informed by data from the pilot study, known only to the study statisticians and DMEC. We utilised one-sided testing (p = 0.05) since we are not trying to prove that the new treatment is better than the standard, and gain considerable statistical efficiency [36]. Power was be set at 80% according to Food and Drug Administration (FDA) recommendations for bioequivalence studies [37].

Based on the mean difference observed between the groups of 2.6 points in the first 71 participants from the pilot study, pooled standard deviation of 16.2, an equivalence margin of +/- 6 points on the Olerud & Molander Ankle Score, yields a final sample size of 560 in total [36]. We inflated for loss to follow up of near 10% yielding a total sample size of 620. Published estimates to inform the selection of equivalence margins using the Olerud & Molander Score was non-existent. Using the pilot data to calculate standardised effects sizes, the equivalence margin includes small differences (<0.37) but excludes moderate or large treatment differences. This was consistent with clinical opinion supporting a 6 point margin excluding clinically important differences in this condition gathered in an informal survey of orthopaedic surgeons, and published data on the minimally clinically important differences for similar scores (Foot and Ankle Score, and visual analogue pain scores in acute injury) that report minimally clinically important differences greater than 10 points on a 100 point scale.

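### No rule says whether the per-protocol or the ITT confidence interval decides equivalence, so it could be claimed on a treatment-received set that is open to arm-specific selection

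*Protocol article*

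**What the plan says.** All references are to the protocol article.

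- **Order and definition of the analyses (Analysis of endpoints).** "Initially, a per-protocol analysis will be undertaken where only the patients who received their allocated treatment will be analysed"; patients who did not receive it are excluded. An ITT analysis of everyone randomised, in the arm they were randomised to, comes next. The pair is justified by regulatory advice and by the risk that ITT used alone can favour a false claim of equivalence.
- **Decision (same section).** Three possible results are listed for a single confidence interval set against the equivalence range, although two analyses are planned. The text continues: "As well as assessing if equivalence is demonstrated in either case", the results will also feed a sensitivity analysis of bias from loss to follow-up, deviations and withdrawal. Nothing says that both analyses must agree or which one prevails.
- **Expected departures from allocation (Intervention, section on manipulation and application of the Close Contact Cast).** In the CCC arm, "a fracture may prove irreducible by closed manipulation. The surgeon would necessarily proceed to open surgical reduction". For patients randomised to ORIF, "The ankle skin condition may have deteriorated such that the surgeon considers one or all necessary surgical incisions to be unsafe", and another treatment is then given. The section also foresees loss of position after either treatment and before healing.

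**The concern.** The per-protocol set is defined by an event after randomisation, and the expected reasons for leaving it are prognostic and specific to each arm. A CCC patient whose fracture cannot be reduced closed leaves the set; a comparable patient randomised to ORIF is fixed as planned and stays. An ORIF patient whose skin makes incision unsafe leaves; a comparable CCC patient stays. The groups that remain are not those that randomisation made comparable.

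The article warns that ITT can mislead in an equivalence trial but does not say that its own per-protocol set can too. This would matter less if both analyses had to agree. As the text stands, the per-protocol interval could lie within ±6 points and the ITT interval not, and the article would not settle what the trial has shown.

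**Working it through.** **Inputs from Sample size.** One-sided 5% level; 80% power; margin ±6 points; "mean difference observed between the groups of 2.6 points in the first 71 participants from the pilot study"; "pooled standard deviation of 16.2"; 560 evaluable, 620 randomised. Allocation 1:1 is assumed, because no ratio is stated.

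**Reproducing the plan's figure.** n per arm = 2 × 16.2² × (1.645 + 0.842)² / (6 − 2.6)², which rounds up to 281, or 562 in total against the stated 560. For loss to follow-up, 560 / 0.90 gives 623 against 620 (560/620 implies 9.7% loss). The sample size reproduces, so 280 per arm and SD 16.2 are used below.

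**Model (assumptions, since the documents give no conversion rates or outcomes).** Let CCC be truly 6 points worse as randomised. A share f of CCC and a share g of ORIF patients are excluded, each scoring D points below those retained in their arm.

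- Per-protocol difference: d = 6 − fD + gD.
- SE = 16.2 × √(1/(280(1−g)) + 1/(280(1−f))).
- Probability that the interval lies within ±6 ≈ Φ((6 − d)/SE − z), with z = 1.645 (90% CI) or 1.96 (95% CI). Both are shown because the sample size uses a one-sided 5% level while the article reports 95% intervals.

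**Worked case: f = 15%, D = 8, g = 0.**

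- Shift = 0.15 × 8 = 1.2, so d = 4.8.
- Retained: 280 ORIF and 238 CCC, 518 in all. SE = 16.2 × √(1/280 + 1/238) ≈ 1.43.
- 90% CI: Φ(1.2/1.43 − 1.645) ≈ 0.21.
- 95% CI: Φ(1.2/1.43 − 1.96) ≈ 0.13.

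**Range.** Chance of declaring equivalence in the per-protocol set:

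| CCC excluded | ORIF excluded | D | d | 90% CI | 95% CI |
|---|---|---|---|---|---|
| 5% | 0 | 10 | 5.50 | 10.0% | 5.5% |
| 10% | 0 | 10 | 5.00 | 17.5% | 10.6% |
| 15% | 0 | 8 | 4.80 | 21% | 13% |
| 20% | 0 | 10 | 4.00 | 39% | 28% |
| 10% | 2% | 10 | 5.20 | 14.0% | 8.2% |
| 10% | 10% | 10 | 6.00 | 5.0% | 2.5% |
| 2% | 10% | 10 | 6.80 | 1.4% | 0.6% |

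In every row the ITT analysis stays at 5.0% / 2.5%.

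**ITT can fail too.** If 10% of CCC patients cross over and gain the ORIF result, a 6-point difference becomes 6 × 0.9 = 5.4. The chance of declaring equivalence by ITT is then about 11% (90% CI) or 6.4% (95% CI).

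**Effect of a decision rule.** A simulation of 200,000 trials per scenario (f = 10% or 20%; D = 10, 15 or 20; g = 0) compared two rules. If either set suffices, the error equals the inflated per-protocol rate. If both must succeed, it returns to about 5.0% / 2.5%.

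**The case against.** The strongest reply has four parts.

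1. *ITT is planned, and per-protocol is nowhere named as primary.* This stands. A reader might infer that failures of casting vanish from the trial, or that the per-protocol analysis is the leading one. The text supports neither: ITT keeps every randomised patient, and the per-protocol analysis is said only to be done initially. What is missing is a statement of which result decides.

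2. *Failures to hold the fracture are not removed.* This also stands. A patient who received CCC and later lost position did receive the allocated treatment, and on the plain reading stays in the set. Only patients who never received their allocation leave. The article does not say so expressly, and one sentence would settle it.

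3. *The direction of bias is unknown.* Correct. ORIF patients are excluded too, equal exclusions with equal deficits cancel the bias, and larger ORIF exclusions make the per-protocol set conservative when CCC is worse. The pilot difference of 2.6 points is given without a direction. A reader might infer that the per-protocol set must favour equivalence; the documents do not show that. An unpredictable direction is still a reason not to let this set decide alone.

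4. *Rules for discordant results belong in the analysis plan, and the wording may simply mean each of the two analyses.* This stands in part. A data analysis plan is to be agreed with the data monitoring committee, and it may contain the rule. But the article itself defines the set, fixes the order and describes how equivalence will be judged. Even if the phrase means each analysis, disagreement between them has no stated consequence.

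**Conclusion.** The concern holds in a limited form. The article plans two analyses, describes one decision and does not join them. One analysis is open to arm-specific selection in either direction and the other to dilution, so neither should carry the claim alone.

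The size depends on assumptions. With 5% to 20% of CCC patients excluded, deficits of 8 to 10 points and no ORIF exclusions, false equivalence in the per-protocol set runs from 10% to 39% (nominal 5%, 90% CI) or from 5.5% to 28% (nominal 2.5%, 95% CI). With 10% excluded from each arm and equal deficits there is no inflation. The documents give no figures to choose between these cases. The finding is therefore that a claim on the per-protocol set alone is left open, not that a false claim is likely.

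**What to change.** In Analysis of endpoints, and in the analysis plan if it does not already say so:

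- Replace the wording that assesses equivalence in either case with a rule: equivalence is concluded only if the confidence interval for the 6-month score difference lies within ±6 points in both the ITT and the per-protocol analysis.
- Keep the per-protocol definition as treatment received, and state that loss of position after the allocated treatment was delivered does not remove a patient from it.
- Report conversions by arm and by reason, so that readers can judge how far the per-protocol set was selected.

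Moving technique-related conversions back into the per-protocol set is not advised. It would make that set nearly identical to ITT and bring back the crossover dilution that the second analysis is meant to guard against.

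**Cost.** Wording, plus coding of the reasons for conversion. The chance of declaring equivalence falls slightly. At a true difference of 2.6 points (90% CI), unbiased exclusion of 10% of CCC patients takes per-protocol power from 80% to 78%, and exclusion of 10% in both arms takes it to 76%. Requiring both analyses cannot exceed the lower of the two powers. The loss would be larger if exclusions moved the per-protocol difference away from zero. The rule also does not protect fully if both analyses are biased towards equivalence at once.

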### Learning and expertise effects

This is a pragmatic study. We will monitor and analyse data to establish the extent, if any, of learning or expertise effects. It is common practice that surgeons have particular expertise in selected techniques, and for surgical teams to organise their workloads so that expertise is utilised to best effect. This study will not interfere with this dynamic. It is therefore not easy to anticipate the direction of expertise and learning effects. For each surgeon participating in the study, we will collect the following information: historical experience and preferences for ORIF and casting, grade of surgeon, time since first operation on the study and, if applicable, years since obtaining a certificate of completion of specialist training. These data will be summarised by recruitment centre and by treatment group and appropriate summary statistics will be produced including tests of association between surgeon experience and the procedures carried out. This will then guide recommendations on implementation and training if the technology proves effective.

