### Randomisation

Randomisation will take place following screening and baseline assessments and the unit of randomisation will be the individual. We will use a remote 24-hour telephone randomisation service, computer generation of the allocation code once the participant is registered, ensures allocation concealment. Randomisation will be stratified by centre and fracture pattern, using infra/trans-syndesmotic (Weber A/B) and supra-syndesmotic categories (Weber C).

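### The primary linear regression makes no allowance for surgeon clustering, so its 95% CI is too narrow to the extent that surgeons work in one arm only

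*Protocol article*

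**What the plan says.** In Analysis of endpoints, the main methods are generalised linear models adjusted for baseline covariates that are not listed. The primary outcome "will be compared between treatment groups as the dependent variable in a linear regression model for the primary analysis", and the treatment difference is reported as adjusted means with 95% confidence intervals. Equivalence is concluded when the interval lies wholly inside the margin, which Sample size gives as "an equivalence margin of +/- 6 points on the Olerud & Molander Ankle Score".

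Learning and expertise effects states that surgeons commonly have expertise in particular techniques, and that it is common "for surgical teams to organise their workloads so that expertise is utilised to best effect. This study will not interfere with this dynamic". Surgeon experience, preference and grade are collected. Their stated use is summaries by centre and by treatment group and tests of association with the procedures carried out; no use in the primary model is mentioned.

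Under Randomisation, "Randomisation will be stratified by centre and fracture pattern". Surgeon is not a stratification factor.

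**The concern.** Patients treated by the same surgeon share that surgeon's choices. The article leaves the method of closed reduction, the choice of implant and the post-operative plan, including progression of weight-bearing, to the individual surgeon. Their scores may therefore be correlated.

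If each surgeon treats both arms, a shared surgeon effect largely cancels from the treatment contrast. If surgeons treat one arm only, it does not cancel: it adds variance to the difference between arms that an ordinary regression does not count. A centre term does not remove it, because the surgeons differ between arms within each centre.

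The direction matters in this trial. Equivalence is claimed when the interval is short enough to fit inside the margin, so an understated standard error pushes towards the conclusion that the trial hopes to reach.

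**Working it through.** **Inputs from Sample size:** margin 6, SD 16.2, assumed true difference 2.6, one-sided alpha 0.05, power 80%, 560 evaluable patients. The number of hospitals (at least 20) is in Summary of study design. An equal allocation ratio is assumed, giving 280 per arm.

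**Step 1. Reproduce the plan's figure.** With independent patients,

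n per arm = 2 × 16.2² × (1.645 + 0.842)² / (6 − 2.6)² ≈ 280.7, rounded up to 281, or 562 in total against the stated 560.

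The stated size is therefore the independent-patients figure, with no clustering allowance in it.

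**Step 2. Baseline precision.** SE = 16.2 × √(2/280) = 1.369. The 95% half-width is 1.960 × 1.369 = 2.68.

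**Step 3. Assumptions.** The article gives neither an ICC nor a caseload. I take an ICC of 0.02 to 0.05, 3 to 7 patients per surgeon (m), and full nesting of surgeons in arms. The upper caseload is 560/20 = 28 evaluable patients per centre, 14 per arm, shared by two surgeons.

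**Step 4. Formulas.** Design effect DE = 1 + (m − 1) × ICC. Correct SE = 1.369 × √DE. One-sided false-equivalence rate at a true difference of 6 = 1 − Φ(z/√DE), with z = 1.960 for a 95% CI and 1.645 for a 90% CI.

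| m | ICC | DE | Correct SE | Correct 95% half-width | Coverage of the model's 95% CI | False equivalence, 95% CI | False equivalence, 90% CI |
|---|---|---|---|---|---|---|---|
| 3 | 0.02 | 1.04 | 1.396 | 2.74 | 94.5% | 2.7% | 5.3% |
| 3 | 0.05 | 1.10 | 1.436 | 2.81 | 93.8% | 3.1% | 5.8% |
| 5 | 0.02 | 1.08 | 1.423 | 2.79 | 94.1% | 3.0% | 5.7% |
| 5 | 0.05 | 1.20 | 1.500 | 2.94 | 92.6% | 3.7% | 6.7% |
| 7 | 0.02 | 1.12 | 1.449 | 2.84 | 93.6% | 3.2% | 6.0% |
| 7 | 0.05 | 1.30 | 1.561 | 3.06 | 91.4% | 4.3% | 7.5% |

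The model SE is 1/√DE of the correct one: from 1/√1.04 = 0.98 to 1/√1.30 = 0.88, or 2% to 12% too small.

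**Step 5. Threshold.** With a 95% CI the one-sided error passes 5% only when DE exceeds (1.960/1.645)² ≈ 1.42. With 7 patients per surgeon that needs an ICC of 0.42/6 = 0.07, above the assumed range.

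**Step 6. Simulation with centre in the model.** I used 20 centres of 28 patients, ordinary regression with fixed centre effects, a true difference of 6 and 6,000 runs per setting. Patients were assigned at random among the available surgeons, so caseloads varied.

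| Surgeons per centre | ICC | True SE | Model SE | False equivalence, 95% CI | False equivalence, 90% CI |
|---|---|---|---|---|---|
| 2 per arm, arm-specific | 0.02 | 1.47 | 1.37 | 3.5% | 6.2% |
| 2 per arm, arm-specific | 0.05 | 1.58 | 1.36 | 4.8% | 7.8% |
| 4 per arm, arm-specific | 0.02 | 1.40 | 1.37 | 3.0% | 5.8% |
| 4 per arm, arm-specific | 0.05 | 1.48 | 1.36 | 3.6% | 6.5% |
| 4 in all, both arms | 0.05 | 1.35 | 1.36 | 2.4% | 4.9% |
| 8 in all, both arms | 0.05 | 1.36 | 1.36 | 2.4% | 4.8% |

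Centre adjustment does not cure the problem when surgeons are arm-specific, and there is no problem when they treat both arms. The 4.8% lies a little above the closed-form 4.3%. Its Monte Carlo standard error is √(0.048 × 0.952/6000) ≈ 0.3 percentage points, and uneven caseloads raise the design effect.

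**The case against.** Four objections deserve an answer.

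- **The detail may be in the analysis plan.** The article says that a data analysis plan will be agreed with the monitoring committee, and that plan could contain a surgeon term. One cannot say that the trial will ignore clustering. What stands is that the article positively names the primary model, names it without such a term, and describes a mechanism that makes the omission matter.

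- **Separation of surgeons by arm is not stated.** The article says that the techniques lie within the expertise of UK-trained surgeons, provides casting training for surgeons, and expects a failed closed reduction to go on to open fixation in the same session. All this is compatible with surgeons working in both arms, where the error stays nominal. A reader might infer from the workload sentence that surgeons will be arm-specific; the text only permits it. The objection stands as a limit on the size of the effect. It does not remove the point, because nothing in the article prevents specialisation.

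- **The 95% interval gives slack.** A reader might infer that false equivalence exceeds the 5% design level. Over the assumed range that happens only with a 90% interval (5.3% to 7.5%), and the article names only 95% intervals. This objection stands. The interval still falls short of its own stated level.

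- **Power.** A reader might also charge the model with a loss of power. Clustering lowers the power of any valid analysis; the model choice does not cause that loss. With the stated 95% interval, power at a difference of 2.6 is already about 70% with independent patients.

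**Conclusion.** The point holds in a conditional and modest form. The named primary model makes no allowance for surgeon clustering, and the trial leaves surgeons free to specialise by technique. To the extent that they do so within centres, the 95% CI is narrower than its nominal level, in the direction that favours equivalence.

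Under full nesting, an ICC of 0.02 to 0.05 and 3 to 7 patients per surgeon, the design effect is about 1.04 to 1.30, and the one-sided error with the stated interval is about 2.7% to 4.3% instead of 2.5%. That is below the 5% design alpha, although the simulated case with uneven caseloads comes close to it at 4.8%. Partial nesting gives less, and surgeons working in both arms give no inflation. All of these sizes rest on the assumed ICC and caseload, because the article supplies neither. It is worth correcting because the remedy is cheap and the error runs the wrong way for an equivalence trial.

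**What to change.** State the primary model as a linear mixed model for the 6-month score, with treatment, the two stratification factors (centre and fracture pattern) and the chosen baseline covariates as fixed effects, and a random effect for treating surgeon within centre. If sparse caseloads make this unstable, use standard errors clustered by surgeon, and fix that fallback in advance. Apply the same model to the per-protocol and the intention-to-treat analyses. Report the surgeon ICC by arm and how many surgeons treated one arm only, so that readers can see how far nesting occurred.

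The cost is analysis wording in the data analysis plan, plus a surgeon identifier linked to each patient. That link should be feasible, since information is collected on every participating surgeon and the operating surgeon's experience is part of the theatre data. The CI may be slightly wider, and surgeons with one patient add little information about the surgeon variance.
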